## Abstract

**Background:**

The standard procedure for the planning of transcatheter aortic valve replacement (TAVR) is the combination of echocardiography, coronary angiography, and cardiovascular computed tomography (TAVR-CT) for the exact determination of the aortic valve dimensions, valve size, and implantation route. However, up to 80% of the patients undergoing TAVR suffer from chronic renal insufficiency. Alternatives to reduce the need for iodinated contrast agents are desirable. Cardiac magnetic resonance (CMR) imaging recently has emerged as such an alternative. Therefore, we aim to investigate, for the first time, the non-inferiority of TAVR-CMR to TAVR-CT regarding efficacy and safety end-points.

**Methods:**

This is a prospective, randomized, open-label trial. It is planned to include 250 patients with symptomatic severe aortic stenosis scheduled for TAVR based on a local heart-team decision. Patients will be randomized in a 1:1 fashion to receive a predefined TAVR-CMR protocol or to receive a standard TAVR-CT protocol within 2 weeks after inclusion. Follow-up will be performed at hospital discharge after TAVR and after 1 and 2 years. The primary efficacy outcome is device implantation success at discharge. The secondary endpoints are a combined safety endpoint and a combined clinical efficacy endpoint at baseline and at 1 and 2 years, as well as a comparison of imaging procedure related variables. Endpoint definitions are based on the updated 2012 VARC-2 consensus document.

**Discussion:**

TAVR-CMR might be an alternative to TAVR-CT for planning a TAVR procedure. If proven to be effective and safe, a broader application of TAVR-CMR might reduce the incidence of acute kidney injury after TAVR and thus improve outcomes.

**Trial registration:**

The trial is registered at ClinicalTrials.gov (NCT03831087). The results will be disseminated at scientific meetings and publication in peer-reviewed journals.

## Administrative information

*Note*: the numbers in curly brackets in this protocol refer to SPIRIT checklist item numbers. The order of the items has been modified to group similar items (see http://www.equator-network.org/reporting-guidelines/spirit-2013-statement-defining-standard-protocol-items-for-clinical-trials/).

## Introduction

### Background and rationale {6a}

Severe aortic stenosis is defined as an aortic valve area (AVA) of ≤ 1.0cm^2^ and a mean transaortic valve gradient of ≤ 40 mmHg [1]. The treatment of symptomatic patients with aortic valve replacement (AVR) is an accepted and well validated [2–6] class I B indication in ESC and ACC/AHA guidelines [1, 7]. Recent randomized controlled trials have proven the benefits of transcatheter aortic valve replacement (TAVR) in patients with symptomatic severe aortic stenosis and intermediate to very-high surgical risk [8–10]. Accordingly, the most recent guidelines recommend TAVR in patients with severe symptomatic aortic stenosis and a predicted life expectancy > 12 months with a class I B if surgical risk is prohibitive and a class IIa C indication if patients are at high surgical risk [7]. The decision for TAVR must be based on the agreement of the “Heart Valve Team” [1]. Since its introduction, more than 350,000 patients have undergone TAVR and its utilization rapidly increases. In some countries more than 50% of isolated AVRs are performed via transcatheter techniques [11].

The standard procedure for the evaluation of patients for TAVR is the combination of transthoracic and transesophageal echocardiography (TTE and TEE), coronary angiography, and cardiovascular computed tomography (TAVR-CT) for the exact determination of the aortic valve dimensions, valve size, and implantation route [12]. This approach is based on the use of ionated contrast agents in three different occasions (angiography, CT, and implantation). However, up to 80% of the patients undergoing TAVR suffer from chronic renal insufficiency [13]. Reduced renal function and the amount of contrast agent used for CT have been linked to contrast induced acute kidney injury [14]. Acute kidney injury occurs in 12% of TAVR procedures and is an independent predictor of in-hospital mortality (odds ratio (OR): 4.14, CI 1.42–12.13) [15]. In Austria, 1426 (~ 17/100,000/year) TAVR procedures were performed in 2019 [16] and 24,386 (~ 29/100,000/year) TAVRs were performed in Germany in 2019, respectively [17]. Based on this data more than 17,000 patients with impaired renal function undergo TAVR each year in Austria and Germany. It can be estimated that nigh on 3000 of these patients will suffer from periprocedural acute kidney injury. As recent data have shown that 3% need in-hospital renal replacement therapy and 2% need chronic renal replacement therapy 6 months after TAVR, this sums up to 750 and 500 patients per year [18, 19]. Therefore, alternatives to reduce the need for iodinated contrast agents are desirable [20, 21]. Cardiac magnetic resonance (CMR) imaging recently has emerged as such an alternative [22, 23].

La Manna et al. investigated 49 patients that were planned to undergo TAVR with TEE and cine steady-state free precession (SSFP) CMR and found a moderate correlation of both methods (*r*^2^: 0.58) regarding aortic annulus size and CMR showed a significant trend to overestimation (TEE 21.4 ± 1.9 mm CMR: 23.7 ± 2.2 mm) [22]. However, annulus sizing was only performed in one dimension in this study. Jabbour et al. investigated 202 consecutive patients, which were scheduled for TAVR with CMR, CT, and TEE and demonstrated a small bias between CMR and CT (0.39 mm) but a large bias between CMR or CT and TEE (4.52 mm and 4.1 mm) for the largest aortic valve (AV) annulus diameter. The authors conclude that CMR and CT are both reliable methods for the sizing of the AV annulus before TAVR [24]. However, in this study, no assessment of peripheral arteries and vascular access routes has been performed. To study the impact of calcification on the agreement of CMR and CT for the sizing of the aortic annulus, Tsang et al. performed ex vivo scans on calcium containing aortic rings and demonstrated that CMR and CT both have a very good correlation with known ring diameters and near zero biases. CMR, however, had smaller limits of agreement than CT (− 0.94 to 1.30 versus − 1.08 to 1.79). Furthermore, an increase in calcification leads to an increase in measurement variability for TEE and CT [25]. Koos et al. compared CMR and CT in 58 patients which were evaluated for TAVR and found no relevant difference between CMR and CT regarding annulus diameter (23.4 ± 1.8 mm and 23.6 ± 1.8 mm, *p* = 0.86), left coronary ostial height (13.2 ± 1.8 mm and 13.3 ± 1.7 mm, *p* = 0.86), and the length of the left coronary leaflet (12.3 ± 1.4 mm and 12.3 ± 1.4 mm, *p* = 0.81). The authors conclude however, “in absence of gold standard a randomized prospective study may give insight into the imaging modality resulting in best procedural outcome” [26]. Recently, Ruile at el. investigated the aortic roots of 69 patients who underwent pre-TAVR CT with 3D non-contrast fast low angle shot (FLASH) CMR and found good agreement of both methods regarding the measurement of aortic annulus area (intraclass correlation 0.961) as well as the distance to the right and left coronary artery (intraclass correlation 0.894 and 0.797) [27]. Promising results have been achieved by Renker et al. in 10 healthy volunteers when comparing a non-contrast self-navigated 3D sequence to a standard 2D-SSFP CMR protocol to study aortic dimensions form the aortic root to the iliac arteries. This study promises a completely contrast-free CMR protocol for the planning of valve size and access routes before TAVR. Although currently the transfemoral approach is predominantly in use, CMR could also be a promising tool enabling to plan TAVR via alternate access routes [28]. However, further feasibility studies in patients with aortic stenosis and calcified peripheral vessels are needed [28]. Novel approaches even utilize real-time CMR for the guidance of TAVR and report easy and effective deployment with the use of the CoreValve and a minimally modified catheter system, which opens the field for a further reduction in contrast and radiation dose during the course of a TAVR procedure [29, 30]. Furthermore, the use of CMR in patients with degenerated bioprosthetic aortic valves before TAVR was shown to be feasible [31].

We have previously presented a fully CMR-guided approach to TAVR planning including aortic root sizing, determination of ostial and leaflet distances, and the evaluation of peripheral vascular access routes [32]. Moreover, we showed for the first time the feasibility of a completely non-contrast enhanced CMR protocol and presented a prototype, navigator-free “whole-heart” CMR angiography for TAVR planning [33, 34]. According to the presented data, CMR is considered as a safe alternative to CT and TEE in the planning of TAVR procedures by leading experts in the field [12, 35, 36]. However, no randomized trial has shown the non-inferiority of CMR to CT in terms of efficacy and safety.

### Objectives {7}

The primary objective of the present study is (a) to prove the non-inferiority of TAVR-CMR compared to TAVR-CT to plan TAVR according to clinical efficacy, defined as implantation success based on the VARC-2 criteria [37]. Secondary objectives are to prove the non-inferiority of TAVR-CMR compared to TAVR-CT to plan TAVR with regard to (b) a combined safety endpoint, based on the VARC-2 criteria [37]. Furthermore, (c) an extended clinical efficacy and safety follow-up for the non-inferiority of TAVR-CMR versus CT after 2 years as well as (d) assess imaging procedure related variables and (e) to study the accuracy of TAVR-CMR and TAVR-CT for the evaluation of patients undergoing TAVR compared to TAVR-TEE measurements.

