#### Secondary endpoints

Secondary end-points consist of clinical efficacy and safety end-points at discharge and 2 years.

*Combined safety end-point:*
All-cause mortalityAll strokesLife-threatening bleedingAcute kidney injury—stage 2 or 3 (including renal replacement therapy)Coronary artery obstruction requiring interventionMajor vascular complicationsValve-related dysfunction requiring repeat procedure

*Combined clinical efficacy end-point:*
All-cause mortalityAll strokeHospitalization for aortic valve related symptoms or heart failureNYHA class III or IVProsthetic valve related dysfunction (mean gradient > 20 mmHg or regurgitation > mild)

Furthermore, the two imaging strategies will be compared regarding imaging procedure related variables:Percentage of interpretable scans and scoring of image qualityPercentage of patients with need for an alternative imaging methodDuration of imaging and patient comfortCumulative radiation dose during TAVR planningCumulative amount of contrast agent used for TAVR planningImaging related safety parameters as contrast extravasation, allergic reactions, et cetera.

Finally, biomarker levels at baseline as well as at follow-up visits will be investigated.

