### Sample size {14} and recruitment {15}

Sample size estimation for the primary endpoint is based on previous data indicating a rate of 4% of early deaths, 4% of valve regurgitation > mild, and 0.4% of reinterventions after TAVR [10]. Therefore, we estimate an implantation success rate of 92% in both study groups. For a non-inferiority margin of 9%, hence 113 patients per group should be included to achieve a statistical power of 80%. A drop-out rate of 10% is assumed. Therefore, it is planned to include a total of 250 patients in the trial.

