## Statistical methods {20a}

Statistical analysis will be performed with SPSS 26.0. (IBM, Armonk, NY, USA) for Windows.

Statistical analysis will be supervised by an independent statistician from the Department of Medical Statistics, Informatics and Health Economics (Innsbruck Medical University). Normally distributed continuous variables will be presented as mean ± standard deviation, not normally distributed continuous variables as median with corresponding interquartile range (IQR). Categorical variables will be displayed as the number and percentage of patients. Pearson or Spearman correlations will be calculated as appropriate. *χ*^2^-test will be used to compare categorical variables between groups. ANOVA with Bonferroni post hoc testing (if ND) and Mann–Whitney-*U* (if not ND) will be used to determine differences in continuous variables between groups. Time-to-event is defined as time from the TAVR procedure to the date of the first end-point. Kaplan–Meier survival curves will be determined and log-rank comparison will be used between groups. Uni- and multivariate Cox-regression analysis will be used to estimate hazard ratios for all left ventricular variables. Factors with univariate association with the primary end-points with significance < 0.1 will be entered in multivariate analysis. For all data a 2-tailed *p*-value of *p* < 0.05 will be considered to indicate statistical significance. No interim analysis is planned.

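### Secondary safety and 2-year aims are worded as non-inferiority claims, under one unadjusted significance rule that neither orders them nor ties them to the primary result

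*Protocol article*

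**What the plan says.** Objectives {7} gives one primary objective, non-inferiority on implantation success. It continues: "Secondary objectives are to prove the non-inferiority of TAVR-CMR compared to TAVR-CT to plan TAVR with regard to (b) a combined safety endpoint". Item (c) in the same list is "an extended clinical efficacy and safety follow-up for the non-inferiority of TAVR-CMR versus CT after 2 years". The abstract's Background puts the overall aim as "the non-inferiority of TAVR-CMR to TAVR-CT regarding efficacy and safety end-points", so safety stands beside efficacy in the headline aim.

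The Secondary endpoints section fixes the assessment times: "Secondary end-points consist of clinical efficacy and safety end-points at discharge and 2 years". It lists a combined safety and a combined clinical efficacy endpoint.

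The decision rule is in Statistical methods {20a}: "For all data a 2-tailed *p*-value of *p* < 0.05 will be considered to indicate statistical significance". The article does not order the secondary claims, divide the significance level among them, make them depend on the primary, or call them supportive. The one multiplicity step named, a Bonferroni post hoc procedure after ANOVA, concerns continuous variables and does not reach the composite endpoints.

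The only margin is for the primary endpoint: "For a non-inferiority margin of 9%, hence 113 patients per group should be included to achieve a statistical power of 80" per cent.

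**The concern.** A claim of proof needs a known error rate. Here safety, 2-year efficacy and 2-year safety are all framed in non-inferiority terms, and one blanket threshold covers them all. Nothing in the stated rule stops a report that misses the primary, or one of the secondary claims, from presenting another as established.

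The safety claim matters most. The abstract's Discussion makes wider use of CMR planning conditional on its being shown both effective and safe. A false finding on the safety composite would therefore count towards replacing the standard planning scan.

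**Working it through.** **Inputs from the article**
- Success rate 92% in both groups, margin 9 points, 80% power, 113 per group (Sample size {14}).
- Two-tailed 0.05 for all data (Statistical methods {20a}).
- Three secondary non-inferiority claims (Objectives {7}): combined safety (b), 2-year efficacy and 2-year safety (both c). Item (b) carries no time point there; I read it as discharge, since (c) is described as the extension.

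**Assumptions, not in the article**
- Each secondary claim has a valid margin.
- Each true effect lies exactly on its margin.
- The test statistics share a common correlation ρ, varied from 0 to 0.9.

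**Step 1: which per-test level applies?** Reproduce the sample size with n = (z₁₋α + z₀.₈)² × 2p(1−p) / margin².
- One-sided 0.05: (1.645 + 0.842)² × 2 × 0.92 × 0.08 / 0.09² = 112.4, so 113 per group. This matches the article.
- One-sided 0.025: (1.960 + 0.842)² × 0.1472 / 0.0081 = 142.6, so 143 per group. At this level, 113 per group gives 70.3% power.

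The sample size therefore rests on one-sided 0.05. The two-tailed 0.05 rule amounts to one-sided 0.025 for a non-inferiority claim, because only one tail supports that claim. Both levels are carried forward.

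**Step 2: three independent claims.** P(at least one false claim) = 1 − (1 − α)³.
- α = 0.025: 1 − 0.975³ = 7.3%, which is 2.93 times α.
- α = 0.05: 1 − 0.95³ = 14.3%, which is 2.85 times α.
- The ceiling for three tests under any dependence is 3α: 7.5% or 15%.

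**Step 3: correlated claims.** The two composites share all-cause mortality and stroke, their valve-dysfunction components overlap, and the safety composite is assessed twice. Positive correlation is expected. With c = z₁₋α,

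P = 1 − ∫ φ(x) [Φ((c − √ρ·x)/√(1−ρ))]³ dx.

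| Assumed ρ | One-sided 0.025 | Ratio | One-sided 0.05 | Ratio |
|---|---|---|---|---|
| 0 | 7.3% | 2.93 | 14.3% | 2.85 |
| 0.3 | 6.8% | 2.73 | 13.0% | 2.61 |
| 0.5 | 6.3% | 2.51 | 11.8% | 2.37 |
| 0.7 | 5.5% | 2.18 | 10.3% | 2.05 |
| 0.9 | 4.2% | 1.67 | 8.0% | 1.59 |

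**Step 4: unequal correlations.** Take correlations of 0.5 between the two safety assessments, 0.3 between discharge safety and 2-year efficacy, and 0.6 between the two 2-year endpoints. Simulation then gives 6.3% (2.52 times) at 0.025 and 12.0% (2.39 times) at 0.05, in line with the ρ = 0.5 row.

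**The case against.** **Ordering of secondary tests usually belongs in the analysis plan, which is not shown.** That is true, and silence alone would not be a finding. Here, however, the article states a rule covering all data and pairs it with an aim of proof. An analysis plan that introduced a hierarchy would have to depart from that sentence.

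**Only (b) is governed by the verb *prove*.** This stands. Item (c) is worded more loosely, and Trial design {8} speaks of extended analysis and follow-up. A reader might infer that the protocol sets out to prove all three claims; the text supports that for (b) only. Item (c) is still listed as a non-inferiority aim, so its status needs settling.

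**No secondary endpoint has a margin, and the tests named are tests of difference.** This also stands. The percentages describe what would happen if valid non-inferiority tests were added, not tests the article already specifies.

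**Larger figures are easy to reach.** A reader might count every two-tailed rejection, but that includes results showing CMR to be worse, which are not false non-inferiority claims. A reader might count six tests by adding the abstract's 1-year assessment, but Trial design {8}, Outcomes {12} and Secondary endpoints do not list that visit. For the three claims in Objectives {7}, the inflation cannot exceed threefold.

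**If efficacy and safety must both succeed, that joint claim is not inflated.** Correct, but nothing in the article makes it a rule.

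**Conclusion.** The point holds as one about the secondary claims. The article frames combined safety as something to be proved, lists 2-year efficacy and safety as non-inferiority aims, and applies one unadjusted threshold without order or dependence on the primary. The primary claim keeps its own error rate.

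The size is moderate. The chance of at least one false secondary claim is about 1.6 to 2.9 times the per-test level. If the stated two-tailed rule is taken at its word, the absolute figure at the highest correlation considered stays below 5%. The larger absolute figures apply only at the one-sided 0.05 implied by the sample size. All figures place every true effect on its margin, which is the worst case, and the correlation is assumed because the article gives none.

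A reader might infer that the ANOVA-related Bonferroni step has no function with two arms and should be deleted. The article does not support this: objective (e) brings in a third modality, TEE, so the step may have a use there.

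**What to change.** In Objectives {7}, reword (b) and (c) as supportive: estimate the difference between groups with a 95% confidence interval, and make no claim that non-inferiority is proven. In Statistical methods {20a}, confine the confirmatory significance rule to the primary endpoint. These are wording changes and need no extra patients or data. The cost is that (b) and (c) can no longer be reported as proven on their own.

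If the sponsor wants to keep a confirmatory safety claim, test it only after the primary has succeeded, at the same level, at one named time point and against a margin justified and stated in advance. That order would hold the error across the primary and safety claims at the single-test level without changing the planned sample size. It is more than a wording change, because a safety margin does not yet exist in the article, and the claim is lost if the primary fails.

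### Non-inferiority is the stated aim for safety and for 2-year outcomes, but the listed analyses are difference tests or hazard-ratio models without a margin; the 1-year time point also conflicts between abstract and body.

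*Protocol article*

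**What the plan says.** **Aims.** In Objectives {7}, item (b) reads "Secondary objectives are to prove the non-inferiority of TAVR-CMR compared to TAVR-CT to plan TAVR with regard to" a combined safety endpoint. Item (c) adds "an extended clinical efficacy and safety follow-up for the non-inferiority of TAVR-CMR versus CT after 2 years". The abstract's Background also names non-inferiority for both efficacy and safety as what the trial will investigate.

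**Margin and sample size.** Sample size {14} and recruitment {15} is confined to the primary endpoint: "Sample size estimation for the primary endpoint is based on previous data", then "we estimate an implantation success rate of 92% in both study groups", then "For a non-inferiority margin of 9%, hence 113 patients per group should be included to achieve a statistical power of 80" per cent. No other margin appears in the article.

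**Analysis.** Statistical methods {20a} gives the chi-square test for categorical variables. For time-to-event outcomes, "Kaplan–Meier survival curves will be determined and log-rank comparison will be used between groups". Cox regression is described for left ventricular variables and for selecting predictors. One two-sided 5% significance level covers everything. No comparison against a margin and no confidence-interval rule is given.

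**Time points.** The abstract's Methods paragraph says "The secondary endpoints are a combined safety endpoint and a combined clinical efficacy endpoint at baseline and at 1 and 2 years", with follow-up visits at discharge, 1 year and 2 years. The body says "Secondary end-points consist of clinical efficacy and safety end-points at discharge and 2 years". Outcomes {12} gives the same two visits, and Trial design {8} places the extended follow-up at 2 years.

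**The concern.** A non-inferiority conclusion needs a margin and a rule that compares a confidence limit, or a shifted test statistic, with that margin. The chi-square and log-rank tests ask whether the arms are equal. A hazard-ratio model gives an estimate, but without a margin there is nothing to judge it against. The aims in Objectives {7} and the tools in Statistical methods {20a} therefore do not meet.

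Safety is not a side issue here. The Background section presents the lack of randomised non-inferiority evidence on efficacy and safety as the gap to be filled. If the final report has only difference tests for these endpoints, the risk is that a non-significant p-value is read as reassurance. With 113 patients per arm, that result is likely even when CMR planning is materially worse.

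The time points matter for a related reason. Whether a 1-year assessment exists decides which comparisons the trial will report on these endpoints.

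**Working it through.** **Inputs from the article:** success 92% in both groups, margin 9 points, power 80%, 113 per group (2 × 113 = 226 analysed), 1:1 allocation, two-sided 5% significance.

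**Assumed, because the article gives no rate for either composite:** 20-30% of patients with an event and, for the log-rank test, a true hazard ratio (CMR versus CT) of 1.5 or 1.3.

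**1. The plan's own figure.** n per group = (z₁₋α + z₀.₈)² × 2p(1−p) / margin², with 2p(1−p) = 2 × 0.92 × 0.08 = 0.1472 and margin² = 0.0081.
- One-sided 5%: (1.645 + 0.842)² × 0.1472 / 0.0081 gives **113**, an exact match (power 80.2%).
- One-sided 2.5%: (1.960 + 0.842)² × 0.1472 / 0.0081 gives 143, no match (power at 113 is 70.3%).

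The stated figure is thus reproduced for implantation success, at one-sided 5%. Both levels are carried forward below.

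**2. How often a log-rank test would miss a worse CMR arm.** SE(log HR) = 2/√d, with d the total number of events.
- 20% of 226: d = 45.2, SE = 0.297. 30% of 226: d = 67.8, SE = 0.243.
- P(non-significant) = Φ(1.96 − log HR/SE) − Φ(−1.96 − log HR/SE).

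| True HR | 20% events | 30% events |
|---|---|---|
| 1.5 | 72% | 61% |
| 1.3 | 86% | 81% |

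**3. The same for a yes/no composite under chi-square.** With 113 per arm and CMR truly 9 points worse, the two-sided 5% test is non-significant in 65.1% of trials at a control rate of 20% and in 70.5% at 30%. Over control rates of 10-40% the range is 52-73%.

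**4. What a non-inferiority test would achieve if the 9-point margin were borrowed.** SE = √(2p(1−p)/113); power = Φ(0.09/SE − z₁₋α); smallest margin at 80% power = (z₁₋α + z₀.₈) × SE.

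| Event rate | SE | 95% CI half-width | Power, one-sided 2.5% | Power, one-sided 5% | Smallest margin at 80% power (2.5% / 5%) |
|---|---|---|---|---|---|
| 20% | 0.0532 | 10.4 points | 39% | 52% | 14.9 / 13.2 points |
| 30% | 0.0610 | 11.9 points | 31% | 43% | 17.1 / 15.2 points |

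On the hazard-ratio scale, the smallest margin testable with 80% power is exp[(z₁₋α + z₀.₈) × 2/√d]. This is 2.30 (20% events) and 1.97 (30%) at one-sided 2.5%, or 2.10 and 1.83 at one-sided 5%.

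**5. Time points side by side.**

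| Place | Secondary composites or visits |
|---|---|
| Abstract, Methods (composites) | baseline, 1 year, 2 years |
| Abstract, Methods (visits) | discharge, 1 year, 2 years |
| Trial design {8} | before discharge (primary); 2 years (extended) |
| Outcomes {12} | discharge, 2 years |
| Secondary endpoints | discharge, 2 years |

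The difference of substance is the 1-year assessment. A composite of post-procedural events cannot be measured at baseline, so that word is best read as a slip for discharge.

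**The case against.** **A secondary margin may stand elsewhere.** The article condenses a full protocol, and a statistical analysis plan may exist. This is fair: a missing margin alone would not be a finding. What stands is a mismatch in what is printed, namely non-inferiority aims alongside a list of difference-type methods under a single two-sided significance level.

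**The log-rank test is not assigned to these endpoints.** Correct. A reader might infer that it is the named test for safety and 2-year outcomes, but Statistical methods {20a} ties it to no particular endpoint. A yes/no composite at discharge would fall under chi-square. That is also a test of difference, so the mismatch is the same whichever applies.

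**The plan does not say that non-significance means non-inferiority.** Also correct. A reader might infer that decision rule because the listed methods offer no other route to the conclusion, but no section states it. The percentages in steps 2 and 3 show how weak such a reading would be. They do not describe a rule in the plan.

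**The word for proving governs only item (b).** True; item (c) speaks of follow-up for non-inferiority. Both are still non-inferiority aims.

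**The event rates and hazard ratios are assumed.** They are, and whether a hazard ratio of 1.3 counts as materially worse is a judgement. The conclusion that the listed tests do not address non-inferiority needs none of these numbers.

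**Table 1 may settle the visits.** It may; it is not reproduced in the text reviewed. The abstract and body would still have to be made to agree.

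**Conclusion.** The point holds as a mismatch between aim and analysis: the methods the article lists cannot support a non-inferiority conclusion for the combined safety endpoint or for 2-year efficacy and safety. It would go too far to say that no such conclusion could ever be supported, since a margin and confidence-interval rule could exist in a document not shown.

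Under assumed event proportions of 20-30% among 226 patients with complete follow-up, a log-rank test would be non-significant in 61-72% of trials at a true hazard ratio of 1.5. A borrowed 9-point margin would have 31-39% power at one-sided 2.5%, or 43-52% at one-sided 5%. The shortfall does not depend on which level is chosen.

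The time-point conflict is real but narrower: it comes down to the 1-year assessment. A reader might take the abstract to plan a composite at baseline, but the visits listed in the same paragraph do not support that reading.

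The point concerns secondary endpoints and leaves the primary comparison untouched. It should be corrected because a safety claim rests on it.

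**What to change.** 1. Reword objectives (b) and (c) as estimating the difference between CMR and CT planning.
2. Report the risk difference with a 95% confidence interval for the yes/no composites at discharge and at 2 years. This suits components recorded at a visit, such as NYHA class and valve gradient. Report the hazard ratio with a 95% confidence interval for time-to-event outcomes.
3. State that no non-inferiority claim will be drawn from a non-significant difference test.
4. Make the abstract, Trial design {8}, Outcomes {12}, Secondary endpoints and Table 1 give one set of time points: correct the baseline entry and decide whether the 1-year assessment is held.

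Keeping the non-inferiority aims is possible in principle, but each would need a justified margin, scale, time point and confidence-interval rule. Under the assumptions above, 113 per arm gives 80% power only for margins of about 13 to 17 points.

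Cost: no additional patients and no change to the primary endpoint. The study was initiated in July 2019, so this is an amendment to be communicated as Protocol amendments {25} requires, including to ethics committees and registries. The small downside is that the secondary safety claim becomes an estimate with its interval.
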